## Abstract

Repetitive transcranial magnetic stimulation (rTMS) of the dorsolateral prefrontal cortex (dlPFC) is currently evolving as an effective and safe therapeutic tool in the treatment of major depressive disorder (MDD). However, already established rTMS treatment paradigms are rather time-consuming. With theta burst stimulation (TBS), a patterned form of rTMS, treatment time can be substantially reduced. Pilot studies and a randomized controlled trial (RCT) demonstrate non-inferiority of TBS to 10 Hz rTMS and support a wider use in MDD. Still, data from placebo-controlled multicenter RCTs are lacking. In this placebo-controlled multicenter study, 236 patients with MDD will be randomized to either intermittent TBS (iTBS) to the left and continuous TBS (cTBS) to the right dlPFC or bilateral sham stimulation (1:1 ratio). The treatment will be performed with 80% resting motor threshold intensity over six consecutive weeks (30 sessions). The primary outcome is the treatment response rate (Montgomery-Asberg Depression Rating Scale reduction ≥ 50%). The aim of the study is to confirm the superiority of active bilateral TBS compared to placebo treatment. In two satellite studies, we intend to identify possible MRI-based and (epi-)genetic predictors of responsiveness to TBS therapy. Positive results will support the clinical use of bilateral TBS as an advantageous, efficient, and well-tolerated treatment and pave the way for further individualization of MDD therapy.

Trial registration: ClinicalTrials.gov (NCT04392947).

## Background

Major depressive disorder (MDD) is one of the leading causes of disease burden, severely impairs quality of life, autonomy, social integration, and life expectancy. Although psychotherapy and medication are effective treatments, a large proportion of patients do not tolerate or sufficiently respond to the initial treatment [1]. Moreover, approximately 50% will experience a recurrent or chronic course of illness for which long-term treatment is recommended [2]. Therefore, the implementation of additional effective and tolerable interventions is highly desirable to expand and individualize treatment options.

In the last two decades, modern noninvasive brain stimulation (NIBS) techniques, particularly repetitive transcranial magnetic stimulation (rTMS), have emerged as effective new means of MDD treatment [3, 4]. Treatment effects are mediated by several mechanisms of action. Among them, left-sided high frequency-rTMS to the left dlPFC increases metabolic activity in connected areas whereas right-sided low frequency-rTMS decreased it [5–7]. In addition, it is suggested that rTMS modulates 5HT_2A_ up- and downregulation in the prefrontal areas and the hippocampus [8]. There are also indications that other neurotransmitter systems (GABA, glutamate) play a role in the effectiveness of rTMS. These different mechanisms lead to changes in functional connectivity in different brain networks [9], which are associated with clinical improvement [10]. Taken together, rTMS treatment strategies of MDD aim at a targeted modulation of dysfunctional cortical activity in prefrontal cortical regions, i.e. the dorsolateral prefrontal cortex (dlPFC) resulting in altered regulation of the respective networks involving subcortical hub regions (e.g. amygdala, subgenual cingulate, and insula) [3, 11–13]. On the behavioral level, the brain network dysfunction is reflected by a preferential perception and processing of negative information subserving the generation and maintenance of depressive symptomatology [14]. Therefore, the targeted modulation of this network by rTMS most likely represents a central neuronal mechanism underlying the beneficial effects of rTMS [15]. Recent meta-analyses agree on medium effect size in respect to response and remission [3, 16]. However, the number of multicenter trials is still rather small and positive full-scaled European trials are missing completely. Moreover, current European treatment guidelines mention rTMS as a treatment option in depression but with a weak grade of recommendation [17]. Hence, this therapy is not available for most patients in Europe and is still restricted to specialized centers or private providers not the least because health insurances do not regularly cover the costs. Therefore, additional evidence for the efficacy of rTMS is required.

However, it has to be considered that lately, theta burst stimulation (TBS) has evolved as an equally effective [18] and considerably less burdening form of rTMS treatment [19]. With TBS, a patterned form of rTMS requiring significantly briefer stimulation sessions and typically lower stimulation intensities, the ‘chair time’ and stimulation-related discomfort is substantially reduced compared to conventional high-frequency rTMS [20, 21]. Moreover, the shorter treatment duration allows for increases in dosage per session, spaced stimulation protocols with multiple stimulations sessions per day, and multifocal, e.g. bilateral stimulation. The pattern-specific modulatory effects of TBS were initially demonstrated in the motor cortex [22] and subsequently investigated for prefrontal cortex regions [23]. In motor regions, continuous TBS (cTBS) predominantly reduced and intermittent TBS (iTBS) increased the excitability of the targeted cortical neurons [24].

However, only a limited number of case series [25–27] and sham-controlled pilot trials with mixed results [28–31] exist investigating TBS of prefrontal cortex regions in terms of its efficacy in MDD. Based on that data, meta-analyses [3, 19, 32, 33] indicate that active TBS (unilateral and bilateral, 2–6 weeks of treatment) is associated with significantly higher response rates when compared to sham TBS. In addition, a large (*n* = 414) multicenter trial demonstrated the non-inferiority of iTBS compared to standard 10 Hz rTMS applied to the left dlPFC [18]. Together, these pilot-studies, meta-analyses and the non-inferiority study support the efficacy of TBS in the treatment of MDD [3, 34]. However, large-scale randomized placebo-controlled clinical trials, especially of bilateral TBS, are still needed [35]. Particularly against the backdrop of the hesitant use of rTMS as a routine depression treatment in Europe, the positive results of the large non-inferiority study [18] are still not sufficient to establish TBS for broader clinical application.

Therefore, the main objective of this clinical trial is to test the efficacy of once-daily, bilateral TBS (cTBS to the right dlPFC and iTBS to the left dlPFC) in a 6 weeks treatment of MDD as add-on to stable ongoing standard therapy. We hypothesize that the number of responders will be significantly higher within the active compared to the placebo TBS group. In addition, we aim to identify biomarkers that allow predicting which patients are most likely to respond to TBS. This aim will be addressed in two associated satellite research projects:

First, by the acquisition of magnetic resonance imaging (MRI) data, we will investigate whether structural MRI as assessed by volumetric T1-weighted images, fiber architecture examined by diffusion MRI or functional connectivity obtained in resting-state functional MRI can be used to predict treatment responses. Based on previous results [36], we hypothesize the dorsolateral prefrontal cortex (dlPFC) as well as the subgenual and rostral anterior cingulate cortex (ACC) as the potential target areas for treatment prediction. We aim to investigate which of the above-mentioned MRI modalities is best suited for treatment prediction and to clarify if their combination by means of multivariate pattern analysis can further improve prediction accuracy.

Second, based on knowledge of genetic predictors of stimulation effects [37–39], it is reasonable to assume that response to bilateral TBS can partially be predicted by multiomics factors, including genetics, epigenetics, and gene expression. However, the systematic investigation of the role of genetic factors as well as the epigenetic regulation of gene expression on TBS response is entirely missing to date. The identification of objective biomarkers with predictive value for treatment success would be highly valuable for clinicians and patients to help tailor personalized treatment options which foster treatment response and long-term remission. For patients that are most likely not benefiting from TBS, other treatment options could be considered early. Having reliable diagnostic biomarkers will hone the efficiency of stimulation treatment for depression and help to minimize treatment costs by choosing effective treatment options for the individual patient.

## Design and methods

This prospective study is designed as a multicenter, randomized, double-blind, placebo-controlled clinical trial and aims to demonstrate the superiority of bilateral theta burst stimulation compared to a placebo condition (i.e. sham TBS) over a 6 weeks treatment period (30 sessions, five per week, daily from Monday to Friday) in patients with MDD.

Altogether 236 patients will be randomly assigned (1:1 ratio) to the two parallel treatment arms. Patients will receive either active combined iTBS/cTBS, or sham iTBS/sham cTBS, respectively. In each session, cTBS will be applied to the right and iTBS to the left dlPFC successively. Active and sham stimulation will be applied as add-on treatment to stable ongoing standard care (psychopharmacological and/or psychotherapeutic therapy). Study assessment with the observer- and self-ratings will be conducted for screening and baseline, after the 2nd, 4th, and 6th week of treatment, and during the follow-up period at two time points (1 and 3 months after end of treatment period).

Two associated satellite projects, entitled ‘MRI-based prediction of TBS-treatment efficacy in MDD’, and ‘Multiomics-analysis based prediction of TBS-treatment efficacy in MDD’ focus on the identification of potential treatment predictors.

This detailed description of the study protocol follows the recommendations of the SPIRIT statement [40].

### Ethics, consent, and registration

Our study will be conducted in accordance with the principles of the Declaration of Helsinki and comply with the guidelines of Good Clinical Practice of the International Conference on Harmonization of Technical Requirements for Registration of Pharmaceuticals for Human Use (ICH). The protocol, patient information, and consent form of this clinical study and its satellite projects have been approved by the Ethics Committee of the Medical Faculty of the University of Tübingen (protocol version 1.0, approved on 31 March 2020 (097/2020BO1) with 1st (22 July 2020) and 2nd (24 February 2021) amendment) and the responsible Ethics Committees of the participating centers. Any significant modifications to the protocol (i.e. concerning study aims, stimulation procedure, inclusion and exclusion criteria, and sample size) will require an amendment that has to be approved by the Ethics Committees of all participating trial sites.

The trial has been registered on http://clinicaltrial.gov (NCT04392947). Trial registration entries will be updated regularly.

### Study population

The clinical trial will include in- and outpatients aged from 18 to 70 years with a primary diagnosis of major depression. Experienced study investigators will perform a clinical interview based on the Diagnostic and Statistical Manual of Mental Disorders 5th Edition (DSM-5). We exclude patients with a duration of illness > 2 years to reduce sample heterogeneity. Table 1 contains all inclusion and exclusion criteria for the present study.

**Table 1 Tab1:** Inclusion and exclusion criteria of TBS-D

Inclusion criteria	
	Age between 18 and 70 years
	Moderate or severe current episode of MDD according to DSM-5 diagnostic criteria
	Duration of current episode of at least 6 weeks but not more than 2 years
	Hamilton Depression Rating Scale (HDRS-17) score of at least 18 (at screening)
	Mild to moderate pharmacological antidepressant treatment resistance according to the short form of Antidepressant Treatment History Form (ATHF-SF); defined as having failed at least one but no more than three adequate antidepressants treatments in the present episode
	Antidepressant medication must be stable at least 4 weeks before the start of treatment intervention (antidepressant medication-free patients can also be included, however patients have to fulfil the criteria of treatment resistance in the current episode)
	Ability to understand the verbal/written study information
	Ability to give consent
	Ability to answer the questions associated with (psychiatric) examination/to fill in the patient self-ratings
Exclusion criteria	
	Acute suicidality (MADRS item 10 score > 4)
	Other psychiatric disorders (except for anxiety disorder)
	Psychotic symptoms
	Intake of antiepileptic drugs or benzodiazepines (corresponding to > 1 mg lorazepam/day)
	Substance dependence or abuse in the past 3 months (with the exception of tobacco)
	Previous rTMS treatment
	Lifetime history of non-response to adequate electroconvulsive therapy (minimum of eight treatments)
	Deep brain stimulation
	History of seizures/brain surgery
	Significant and clinically relevant brain malformation or neoplasm
	Head injury/stroke/dementia or other neurodegenerative disorders
	Cardiac pacemakers, intracranial implant, or ferromagnetic parts in the cranium
	Pregnancy

### Study centers and recruitment

Besides the Department of Psychiatry and Psychotherapy of the University of Tübingen (coordinating center) six additional psychiatric departments in Germany will participate in the study. These centers must have the appropriate technical equipment (see below ‘Technical Devices’) and experienced staff (at least 6 months) regarding TMS treatment of depressive patients. Furthermore, the study protocol will be approved by the respective institutional ethics committees before site initiation.

All centers will recruit patients in their in- and outpatient clinics. In addition, all study centers can address potential candidates by contacting (1) local patient advocacy/support groups, (2) local psychiatrists/general practitioners, as well as (3) information via clinic website, social media, newsletters, local newspapers, or advertisement in public transportation.

During the initial phase of the recruitment process, i.e. the pre-screening period, a study investigator will give comprehensive verbal and written information about trial-related objective, procedures, and possible risks to each patient and if necessary to the legal representatives, too. All patients will have the opportunity to ask questions and will have enough time to consider whether they want to participate in the study. Before any study-specific measures can be administered, a signed consent form must be present.

Continuous site monitoring will ensure the early identification of recruitment problems. In cases of relevant delays, site-specific measures will be taken, e.g. additional dedicated staff, alternative organizational structures, intensified social media activity, and further involvement of local patient groups. However, in case of persistent and substantial recruitment delays, the study center will be closed and a suitable new center will be identified and initiated.

### Patient involvement

To ensure patient participation, the coordinating center cooperates with the nationwide patient advocacy group Deutsche DepressionsLiga (DDL, https://www.depressionsliga.de) and the Stiftung Deutsche Depressionshilfe (https://www.deutsche-depressionshilfe.de), which is a member of the European Alliance against Depression. Both organizations will support recruitment and help to disseminate information about the study and its results to the public. The DDL is especially dedicated to protecting the interests of patients within this study, acting as a forum for concerns and expectations related to TMS treatment.

### Study timeline

Figure 1 gives a overview of the study timeline. Once the signed consent form is available, the pre-treatment phase can start with the screening process (for details see “Assessment” or Table 2). As soon as it becomes evident that a patient does not meet the criteria for study participation (Table 1), all study-specific procedures will be stopped and participation in the study will end. Patients who meet the inclusion and exclusion criteria will be randomized either to the verum or placebo group. In a next step, patients will participate in the baseline session (Table 2), including MRI measurements and blood samples for patients who participate in the respective satellite-studies.

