**Fig. 1 Fig1:**
[figure not shown]
Trial flow

**Table 2 Tab2:** Study flow chart

	Study period												
	Pre-Treatment		Treatment									Follow-up	
Week	0		1	2		3	4		5	6		10	18
Visit	Screening	Baseline	V1-V5	V6-V10	V10	V11-V15	V16-V20	V20	V21-V25	V26-V30	V30	V31	V32
Informed consent	X												
Sociodemography	X												
Pregnancy test^1^	X												
Physical/neurological examination	X												
Concomitant treatment^2^	X	X			X			X			X	X	X
SCID-5-PD	X												
ATHF-SF	X												
MADRS (item 10 only)	X												
HDRS-17	X				X			X			X	X	X
Randomization	X												
MADRS (complete)		X			X			X			X	X	X
BDI-II		X			X			X			X	X	X
CGI		X			X			X			X	X	X
WHO-5		X									X	X	X
WPAI		X									X		X
THINC-it^®^ (test of cognition)		X									X		X
CTQ		X											
EHI		X											
MRI^3^		X											
Genetics^3^		X									X		X
Determination of resting motor threshold^4^		X											
Active iTBS/cTBS sham iTBS/cTBS													
Safety check													

^1^Pregnancy test is only necessary for women in child-bearing age; if a blood sample is taken as part of the clinical routine, it is advisable to check a possible pregnancy with a blood test. Otherwise, a urine test can be used to avoid unnecessary risks

^2^Concomitant medication and/or any type of psychotherapy will be documented for each patient for his/her entire participation period

^3^MRI and Genetics are not part of the standard protocol but belong to two satellite projects

^4^Alternatively, the threshold can also be determined directly before the first stimulation, i.e. in visit 1

Study treatment will start on Monday within the week after completion of the baseline session (deviations in case of holidays are possible). During the treatment phase, each patient will receive a total of 30 TBS sessions over a period of 6 consecutive weeks (one session daily from Monday to Friday).

Ratings will take place at the end of the 2nd, 4th, and 6th weeks after the respective stimulation session.

Within the follow-up period two visits are scheduled, 1 month and 3 months after the end of treatment. Patient participation in the study will end with last follow-up.

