### Randomization

The Institute of Clinical Epidemiology and Applied Biostatistics of the University of Tübingen (IKEaB) is responsible for randomization. By using the randomization tool of the software nQuery (release 8), patients will be allocated either to the active or placebo group in 1:1 ratio with varying block lengths. Additionally, the order of cTBS and iTBS in the first session (cTBS–iTBS or iTBS–cTBS, respectively) will be randomized and subsequently alternated in all following sessions. Randomization is stratified for the study center.

Technically, the IKEaB will receive a list with patient keys (6-digit numerical codes) provided by the manufacturer of the magnetic stimulator (MagVenture^©^, Farum, Denmark). These patient keys must be entered into the magnetic stimulator to start the stimulation session and determine whether the machine delivers verum or sham stimulation (for details see “Intervention”). Each patient key will be used only once during the entire trial and each randomized patient will keep his/her patient key until the end of treatment. The patient keys are matched to the randomization list obtained from the software nQuery by using the statistical software SPSS. This will be done by an independent statistician not involved in the study.

The study centers will receive only the patient keys together with the information about the order of iTBS and cTBS on demand by using the computerized randomization tool of our database secuTrial^®^. The patient key itself cannot be used to identify the treatment arm, thus ensuring blinding of study physicians, TMS-operators, patients, and data analysing statistician.

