### Sample size calculation

In an own pilot study (*n* = 32) we found 9/16 (56%) responders (MADRS ≤ 50% of baseline) in the verum group and 4/16 (25%) responders in the sham group [28]. In a second pilot study (*n* = 60) of another group [29] response rates (HDRS-17 ≤ 50% of baseline) were 66.7% vs. 13.3% after 2 weeks treatment and 4/15 (27%) vs. 1/15 (7%) after week 14. In the third pilot study (*n* = 56) [30] response rates (HDRS-17 ≤ 50% of baseline) were 55% (bilateral TBS) and 30% (sham TBS), 7 weeks after initiation of a 3 weeks treatment. In a recent large (total *n* = 385) clinical trial [18] comparing iTBS (*n* = 193) with 10 Hz rTMS (*n* = 192) the outcome criterion of HDRS-17 ≤ 50% of baseline was achieved by 49% of patients treated with iTBS. Based on these studies, we conservatively assume a response rate of 49% vs. 30% (combined bilateral TBS vs. sham TBS) using the criterion MADRS reduction of at least 50% compared to baseline. This leads to a sample size of 103 subjects per group (Chi-square test, alpha = 0.05 two-sided, beta = 0.2), totally 206 evaluable subjects. As we will recruit in seven centers we increase the sample size by *n* = 6 to compensate for degrees of freedom in a stratified analysis which leads to 212 patients. The analysis will be done on the full set of patients except for those refusing consent during the study or not receiving at least one treatment. We expect a low dropout rate and therefore, we increase the sample size by 24 subjects to adjust for 10% dropouts, which leads to a total n of 236 patients.

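### Randomisation at screening, before the baseline session, creates avoidable exclusions between allocation and session 1, and the resulting treated set is labelled ITT

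*Protocol article*

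**What the plan says.** All references are to the protocol article.

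- **Eligibility and allocation.** Study timeline: "Patients who meet the inclusion and exclusion criteria will be randomized either to the verum or placebo group". Table 2 puts the randomisation mark in the Screening column.
- **Baseline comes afterwards.** Study timeline: "In a next step, patients will participate in the baseline session (Table 2), including MRI measurements and blood samples". In Table 2 the complete MADRS, BDI-II, CGI and the satellite MRI stand in the Baseline column. At screening only item 10 of the MADRS is rated.
- **Treatment comes later again.** Text below Table 2: "Study treatment will start on Monday within the week after completion of the baseline session".
- **One criterion is tied to treatment start.** Table 1: "Antidepressant medication must be stable at least 4 weeks before the start of treatment intervention".
- **Release of the allocation.** Randomization: "The study centers will receive only the patient keys together with the information about the order of iTBS and cTBS on demand". The same section says that each key is used once and that the key does not reveal the arm.
- **Analysis set.** Statistical analysis admits to the primary ITT analysis only patients with at least one treatment. Sample size calculation also excludes untreated patients, and additionally those who withdraw consent during the study.
- **Use of the baseline MADRS.** It is the reference for the 50% reduction (Primary outcome measure). It is also a covariate in the logistic model and a predictor in the imputation model (Statistical analysis).

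**The concern.** The sequence is screening, randomisation, baseline session, then session 1. A patient can leave at either of the last two steps, for example by withdrawing or through a change of medication that breaks the stability period. That patient has been allocated, has used a single-use key and a place in a centre's block, and is then removed from the primary analysis. The analysed set is therefore smaller than the randomised set for a reason that the design itself creates.

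The order also makes a full ITT analysis hard to recover. A patient lost before the baseline session has no MADRS total, so the response criterion has no denominator and the model lacks a covariate. Imputation would have to supply the baseline value as well as the outcome.

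What is at stake is the accuracy of the ITT label, how clear the participant flow will be to readers, and part of the 24-patient dropout allowance.

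**Working it through.** **Inputs (Sample size calculation, Design and methods).** Test and error rates: "Chi-square test, alpha = 0.05 two-sided, beta = 0.2". Effect: "a response rate of 49% vs. 30% (combined bilateral TBS vs. sham TBS". Total: "Altogether 236 patients will be randomly assigned (1:1 ratio) to the two parallel treatment arms".

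**1. Reproducing the plan's sample size.** Mean rate = (0.49 + 0.30)/2 = 0.395; difference = 0.19.

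n per group = [1.960·√(2·0.395·0.605) + 0.842·√(0.49·0.51 + 0.30·0.70)]² / 0.19² = (1.355 + 0.571)² / 0.0361 = 102.7, rounded up to 103.

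2 × 103 = 206; 206 + 6 = 212; 212/0.90 = 235.6, rounded up to 236. All the stated figures reproduce.

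**2. Power for n analysed per group.** Power = Φ[(0.19·√n − 1.355)/0.678]. With n = 118 this is Φ(1.045) = 85.2%.

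**3. Assumed loss L between randomisation and session 1.** The article gives no such rate, so 2%, 5% and 10% are assumptions.

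- Column A: untreated patients are excluded and every treated patient counts in full.
- Column B: a further 10% of treated patients drop out and only complete cases count.
- Column C: all 236 are analysed, and untreated patients in the active arm respond at the 30% sham rate.

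| L | Lost (L × 236) | Treated set | A | B | C |
|---|---|---|---|---|---|
| 0% | 0 | 236 | 85.2% | 81.3% | 85.2% |
| 2% | 4.7 | 231.3 | 84.5% | 80.5% | 83.8% |
| 5% | 11.8 | 224.2 | 83.4% | 79.3% | 81.5% |
| 10% | 23.6 | 212.4 | 81.3% | 77.1% | 77.3% |

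The plan keeps on-treatment dropouts through multiple imputation, which recovers some but not all of their information. For the primary analysis as planned, A is therefore an upper bound and B a cautious lower figure.

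**4. The allowance.** If all losses together, before and during treatment, come to 24, then 212 remain and power is 81.2%. With 28 lost it is 80.5%. It falls below 80% at 31 lost (31/236 = 13.1%; power 79.9%). Keeping 212 evaluable after both L and a further 10% would need 212/0.90/(1 − L) randomised: 241, 248 or 262 at L = 2%, 5% or 10%.

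**5. Is the early allocation needed?** The uses of the key described in Randomization and Technical devices are to start stimulation and to fix which condition the coil delivers. The order of the two stimulation types is first used in session 1. The motor threshold is measured with a different coil. Nothing listed for the baseline session in the Assessment section calls for the key.

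**The case against.** A reader might infer three stronger points. The document supports none of them.

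**Patients are randomised before eligibility can be confirmed.** The Study timeline makes meeting the criteria a condition of randomisation. The diagnosis, SCID-5-PD, ATHF-SF, HDRS-17, MADRS item 10, pregnancy test, examination and concomitant treatment are all assessed at screening. No criterion uses the complete MADRS, and the HDRS-17 threshold is explicitly a screening value. The MRI belongs to a satellite project outside the standard protocol, so the brain-lesion criterion does not have to wait for it; an incidental finding is possible, but the article does not say what would follow. The sentence that ends participation for ineligible patients stands before the randomisation sentence and describes screen failures. What remains is narrow: medication stability can be documented at screening but can lapse before session 1.

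**The treatment effect is biased.** The Randomization and Blinding sections keep the arm hidden from patients and staff. Losses before session 1, and the baseline rating itself, should therefore not depend on arm. The exclusion of untreated patients is also stated openly and in advance.

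**The trial is underpowered.** The Sample size calculation states the exclusion directly before adding 24 patients, so these losses can fairly be counted within that allowance. Power then stays above 80%.

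It is also fair to say that block imbalance from a few losses is routine, that centre is in the model, and that nothing suggests keys are scarce. The full operational protocol is not shown and may give a reason for early allocation.

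Against this, three facts stand: the order of events, the missing MADRS denominator for anyone lost before baseline, and the label on the analysis set.

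**Conclusion.** The point holds in a limited form. Randomisation precedes the complete baseline MADRS and the start of treatment. Patients lost in between are removed from an analysis called ITT, which is in fact a modified ITT analysis of treated patients. The cost is avoidable post-randomisation exclusions, an inaccurate label and a small loss of power.

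The size depends on a loss rate that the article does not give. At 2% to 10%, about 5 to 24 patients would be excluded. Power would be 84.5% to 81.3% if imputation lost no information on dropouts, and 80.5% to 77.1% in the harsher case of a further 10% dropout with complete cases only. All power figures use the plan's own chi-square setting and its 49% and 30% response rates, not the adjusted logistic model.

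The order of events and the set definition are certain from the text; the number of patients affected is not. Severity: minor to moderate.

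**What to change.** 1. In Table 2 and the Study timeline, move randomisation to after the complete baseline session and a re-check of the existing eligibility criteria, immediately before the first session.
2. Set secuTrial to release the patient key and first-session order only once the baseline MADRS has been entered and the re-check recorded.
3. For any patients already randomised under the present order, call the primary set modified ITT and report those randomised but untreated by arm, with reasons, after unblinding.
4. Give the set one definition in Sample size calculation and Statistical analysis. At present only the former excludes patients who withdraw consent.

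How a lapse in medication stability is handled is for the trial team to decide; the change concerns only when allocation takes place.

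Simply analysing all randomised patients under the present timing is the less attractive route. It needs imputed baseline values for those lost early, and in column C it costs more power than column A. Later randomisation brings the treated and randomised sets close together.

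Cost: an amendment to the wording, approved by the ethics committees if it counts as a significant modification, and a setting in the randomisation tool. The sample size does not change. The downside is that sites must call the tool shortly before or on the day of session 1.
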